## 3. Expected Results

The results of this study are expected within three years after the project initiation. Based on previous research [13,14,15,16,17,18,19,20], we anticipate that Text4support in Nova Scotia will achieve similar mental health outcomes, with a 20% greater improvement in patients’ recovery and quality of life and a 20% greater reduction in depressive and anxiety symptoms, when assessed by the mean change in validated scale scores at six weeks and three, six, and twelve months from the baseline compared with control interventions. The mean differences in scores obtained from other validated scales that will assess resilience, childhood trauma, substance craving, the presence and severity of psychotic disorders, suicide risk, and manic symptoms are expected to be alike. We also anticipate a 10–25% reduction in high-cost health service use (psychiatric readmissions and ED visits) among Text4Support participants compared with the usual care group. An unpublished pilot trial in Alberta (*n* = 180) found that the patients discharged from inpatient psychiatric units who received Text4Support messages for 6 months made 10% fewer ED visits in the 6 months following discharge than a control population [6]. We anticipate that Text4Support participants will also use fewer high-cost health services in Nova Scotia. In terms of the retention and patient engagement rates, we confidently predict that IG participants will achieve higher figures (at least 80%) than the CG participants’ self-reported retention rate and engagement on e-mental health resources. This optimistic estimation is based on evidence of “push” text message technologies, in which intervention messages are delivered without the individual’s intervention and have a 98% open rate [49]. Additionally, previous research has shown that after six weeks of intervention, the retention rate in similar text messaging programs (Text4Hope) was around 90% [17,18], indicating that subscribers were still opening and reading the messages.

## 4. Risks and Limitations

As with every research study, there is a risk of data identification. To prevent this from happening, all the collected data will be labelled with a unique study ID number. Only the aggregated and de-identified data will be used in publications. Regarding the intervention, the risk to participants is not supported by evidence from our predecessor programs, such as Text4Mood and Text4Hope, but even so, client safety and monitoring protocols will be implemented throughout the trial. The research team will monitor patients through the data collected and notify patients and healthcare providers if the results indicate a potential risk to the patient (e.g., if a patient presents an assessment score compatible with suicidal ideation). In this case, participants will be directed to call a crisis line or go to their local ED if an emergency occurs.

## 5. Conclusions

This study will demonstrate an innovative approach to augmenting mental health support to individuals accessing different degrees of formal psychiatric care in Nova Scotia. The success of Text4Support in the province will not only provide evidence relevant to new stepped care and technology-based approaches to mental health service delivery but will also contribute to the knowledge of how to implement mental health innovations in different clinical contexts, contributing to close the mental health support worldwide.

## Figures and Tables

**Figure 1 mps-06-00019-f001:**
[figure not shown]
Study flow diagram.

**Figure 2 mps-06-00019-f002:**
[figure not shown]
(**a**–**c**): Text4Support general well-being message; Text4Support anxiety message; Text4Support psychosis message.

**Table 1 mps-06-00019-t001:** Text4Support RCT outcomes measures, instruments and data collection time points.

Outcome Measures	Instrument	Description	Data Collection Time Points				
			Baseline	6 w	3 m	6 m	12 m
** *Clinical outcomes (measures of impact)* **							
**Patient’s recovery**	Recovery Assessment Scale (RAS) [37] *	RAS is a 20-item measure developed based on a process model of recovery, which evaluates various aspects of recovery with a special focus on hope and self-determination.	X	X	X	X	X
**Quality of Life**	WHO-5 Well-Being Index [38] *	WHO-5-Well-Being Index is a short 5-item generic global rating scale measuring subjective well-being. The scale was derived from the WHO-10, which in turn was derived from a 28-item rating scale. The scale has adequate validity both as a screening tool for depression and as an outcome measure in clinical trials.	X	X	X	X	X
**Likely depression**	PHQ-9 [39] *	The PHQ-9 is a 9-item validated instrument used to diagnose and measure the severity of depression in general medical and mental health settings. The scale has good convergent validity and adequate internal consistency.	X	X	X	X	X
**Likely anxiety**	GAD-7 [40] *	GAD-7 is a validated 7-item questionnaire used to assess the self-reported levels of anxiety in respondents in the two weeks prior to assessment.	X	X	X	X	X
**Patient’s Resilience**	BRS [41] *	The BRS assesses the perceived ability to bounce back or recover from stress. The possible score range on the BRS is from 1 (low resilience) to 5 (high resilience)	X	X	X	X	X
**Patient’s trauma-related stress**	ACE questionnaire [42] *	The ACE Questionnaire is a 10-item measure used to measure childhood trauma. The questionnaire assesses 10 types of childhood trauma measured in the ACE Study.	X				
**Patient’s tendency and desire for each addictive substance**	BSCS [43] *	BSCS is a self-reporting scale to assess the intensity, frequency, and length of time spent craving in the past 24 h, using a five-point Likert scale ranging from 0 to 4 with a mean score of 0 indicating no cravings in the past 24 h and a mean score of 4 indicating a high tendency for drug craving.	X	X	X	X	X
**Patient’s suicidal risk**	Columbia Rating Scale [44] **	C-SSRS is a self-reporting suicidal ideation and behaviour rating scale to evaluate suicide risk.	X	X	X	X	X
** *Health Services Utilization Outcomes (measures of impact)* **							
**Crisis calls**	Administrative data	The number and proportion of patients calling the Crisis helpline.	-	-	-	-	X
**Hospital Admissions**	Administrative data	The number and proportion of MHA admissions into medical units, specialty, forensic of withdrawal management units in the last 12 months	-	-	-	-	X
**Length of Stay**	Administrative data	Length of stay for each MHA-related hospital admission.	-	-	-	-	X
**Hospital readmissions**	Administrative data	The number and proportion of patients readmitted into MHA acute care units within 30-days after discharge.	-	-	-	-	X
**Emergency Department (ED) presentations**	Administrative data	The number and proportion of MHA-specific ED presentations.					

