### 2.2. Settings and Study Participants

The study will be conducted at mental health and addiction (MHA) outpatient and inpatient services, including community mental health and addiction programs (CMHAPs), specialty programs (SPs), addiction programs (APs), emergency departments (EDs), and psychiatric inpatient units (PIUs), across the province of Nova Scotia, Canada. The recently launched Day Hospital and the Transcultural Mental Health Program, as well as the Rapid Access and Stabilization Program that is expected to be initiated, will be part of the study, totalling 46 study sites. New patients (i.e., first-time users) of MHA outpatient programs and patients being discharged from MHA inpatient facilities (i.e., at most one week prior to their expected discharge date) will be eligible for the study. Additionally, they must be 18 years old or older, have a phone capable of receiving text messages (no data plan is required), be able to read English, and provide written consent. Patients will be disqualified if they are unable to read text messages from a mobile device or are unwilling or unable to grant permission to participate in the trial.

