### 2.6. Outcome Measures

The intervention effectiveness will be determined by evaluating the differences between the intervention and control group from baseline and the subsequent time points (6 weeks and 3, 6, and 12 months) for patient clinical outcomes and the differences between groups for health service utilization at 12 months, and the implementation success will be measured through quantitative and qualitative patient satisfaction data and implementation indicators, as follows:Clinical outcomes: The primary clinical outcome will be the differences in mean change in patient recovery and quality of life, assessed through the Recovery Assessment Scale (RAS) [37] and the World Health Organization Five Well-Being Index (WHO-5) [38]. Secondary clinical outcomes will include the differences between the intervention and control groups in prevalence changes for moderate-to-high depression (likely major depressive disorder), moderate-to-high anxiety (likely generalized anxiety disorder), and low resilience from the baseline to these time points, assessed through the Patient Health Questionnaire-9 (PHQ-9) [39], Generalized Anxiety Disorder-7 scale [40], and the Brief Resilience Scale (BRS) [41]. The mean score differences between groups from the baseline to determine time points will also be assessed using the Adverse Childhood questionnaire (ACE questionnaire) [42], and the Brief Substance Use Craving Scale (BSCS) [43], which will be used to assess childhood trauma and substance craving, as well as the clinician-rated Columbia-Suicide Severity Rating Scale (C-SSRS) [44], which will be used to assess suicide risk.Health service utilization outcomes: Health service utilization data will be extracted by the registration, reporting, and analytics, mental health and addiction team from the multiple health information systems utilized across NS Health and provided to the research team through reports. The differences in health service utilization data (mobile crisis visits, number of ED presentations, number of admissions in the last 12 months, length of stay, and the number of hospital readmissions) will be evaluated for participants in both groups. The differences between groups will be evaluated at 12 months.Patient experience and satisfaction outcomes: Patient satisfaction and patient experience with the e-mental health interventions (Text4Support and other e-mental health programs offered freely through NSH Authority) will be evaluated using both quantitative and qualitative data. Overall satisfaction will be assessed at each of the four time points (6 weeks and 3, 6, and 12 months) using a self-designed scale. Self-reported retention and withdrawal will both be assessed through the satisfaction survey, which addresses questions about the frequency of reading messages, the frequency of returning to messages stored in their phones, and actions taken by the participants after reading the text messages or freely available e-mental health resources (i.e., text “STOP”, clicking on links, searching for more information) up to 12 months after enrolment. Patient experience and satisfaction qualitative data will be collected through individual interviews and focus groups.Implementation Outcomes: Implementation outcomes are indicators of implementation efforts and are distinct from service or clinical outcomes [45]. For the intervention arm, we will include the reach of the interventions, acceptability, appropriateness, fidelity, and cost-effectiveness, evaluated at each of the four time points [28]. These implementation indicators will not be collected from the e-mental health or website visits in the control arm because they are not tied to the patient’s study ID and cannot be linked to the other measures.

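### Length of stay is defined per admission, so the between-arm comparison covers only admitted participants and does not show the direction of any benefit; the index stay, the readmission base and the admission unit list also need fixing.

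*Protocol article*

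**What the plan says.** All of this is in the protocol article. In Table 1, under health services utilization, the length-of-stay row reads "Length of stay for each MHA-related hospital admission". It gives no time window, no rule for a participant without an admission and no rule for a stay already under way at enrolment. Section 2.6 lists length of stay beside ED presentations, admissions and readmissions and says that the differences "will be evaluated for participants in both groups. The differences between groups will be evaluated at 12 months".

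The readmission row is "The number and proportion of patients readmitted into MHA acute care units within 30-days after discharge". It states neither a denominator nor which discharge starts the 30 days. The admissions row is "The number and proportion of MHA admissions into medical units, specialty, forensic of withdrawal management units in the last 12 months".

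Section 2.2 admits participants by two routes. One is "New patients (i.e., first-time users) of MHA outpatient programs". The other is inpatients near discharge: "patients being discharged from MHA inpatient facilities (i.e., at most one week prior to their expected discharge date) will be eligible for the study". Section 2.5 starts the messages a day after enrolment.

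**The concern.** The unit of the length-of-stay measure is the admission. Who contributes a value is decided after randomisation, and admissions are themselves an outcome that the trial hopes to reduce. If the intervention averts some admissions, the admitted participants in the two arms are no longer comparable groups. A difference in mean stay then mixes any effect on how long people stay with the effect on who is admitted. A rise could accompany a real saving in bed-days, and no change could conceal one.

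Three nearby definitions add to this. An inpatient enrolled in the last week before discharge brings an index stay that largely precedes randomisation, and the row does not say whether it counts. The 30-day readmission row does not say among whom, or from which discharge, although one of the two entry routes has no index discharge at enrolment. The units named in the admissions row are not those named in the readmission row.

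**Working it through.** The plan gives no expected stay, admission rate or power for these outcomes, so there is no figure to reproduce. The check is whether the stated measure follows the direction of benefit.

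**Inputs.** From the article: the per-admission definition (Table 1) and the two entry routes (Section 2.2). The 10-25% range is borrowed from Section 3, where it is a forecast for psychiatric readmissions and ED visits; applying it to admissions is an assumption. Also assumed: 20 of 100 control participants admitted once each, half with short and half with long stays, of 7 and 21 days or 5 and 30 days.

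**Formulas.** With S short and L long admissions per 100 randomised, lasting s and l days:
- mean stay per admission = (S·s + L·l)/(S + L)
- bed-days per randomised participant = (S·s + L·l)/100, with non-admitted participants counted as zero

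**Control arm.**
- 7/21 days: (10·7 + 10·21)/20 = 14.0 days; 280/100 = 2.80 bed-days
- 5/30 days: (10·5 + 10·30)/20 = 17.5 days; 350/100 = 3.50 bed-days

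**Intervention arm**, with 2 (10%) or 5 (25%) of the 20 admissions averted. Example, 7/21 days, 5 short stays averted: (5·7 + 10·21)/15 = 245/15 = 16.33 days, against 245/100 = 2.45 bed-days.

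| Stays | Averted | Mean stay, 10% fewer | Mean stay, 25% fewer | Bed-days per randomised, 10% fewer | Bed-days per randomised, 25% fewer |
|---|---|---|---|---|---|
| 7/21 | short only | 14.78 (+5.6%) | 16.33 (+16.7%) | 2.66 (-5.0%) | 2.45 (-12.5%) |
| 7/21 | random mix | 14.00 (0%) | 14.00 (0%) | 2.52 (-10.0%) | 2.10 (-25.0%) |
| 7/21 | long only | 13.22 (-5.6%) | 11.67 (-16.7%) | 2.38 (-15.0%) | 1.75 (-37.5%) |
| 5/30 | short only | 18.89 (+7.9%) | 21.67 (+23.8%) | 3.40 (-2.9%) | 3.25 (-7.1%) |
| 5/30 | random mix | 17.50 (0%) | 17.50 (0%) | 3.15 (-10.0%) | 2.63 (-25.0%) |
| 5/30 | long only | 16.11 (-7.9%) | 13.33 (-23.8%) | 2.90 (-17.1%) | 2.00 (-42.9%) |

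The percentages are the same if 10% or 30% of controls are admitted. Every row is a benefit by construction. Bed-days per randomised participant fall in all of them, while mean stay per admission rises, stays level or falls.

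**Index stay.** Enrolment is at most a week before expected discharge. If discharge is on time, a 21-day index stay has at least 21 - 7 = 14 days before enrolment, and a 30-day stay at least 30 - 7 = 23. Those days cannot respond to the messages. They are expected to be alike in both arms, so including them pulls the difference towards zero.

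**30-day readmission.** The result depends on the base. Suppose (assumed) that readmission risk is 10% after the averted type of admission and 30% after the other, with 20 of 100 controls admitted.
- Among those discharged after randomisation: control (10·0.10 + 10·0.30)/20 = 20.0%; intervention (8·0.10 + 10·0.30)/18 = 21.1%, or (5·0.10 + 10·0.30)/15 = 23.3%.
- Among all randomised: 4.0% against 3.8% or 3.5%.

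On the first base the sign turns; on the second it does not. It also need not turn for participants enrolled near discharge and followed from their index discharge, since that hospital stay began before randomisation.

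**Units.** The admissions row names medical, specialty, forensic and withdrawal management units. The readmission row names MHA acute care units. Section 2.6 counts admissions without any limit on unit, and the length-of-stay row covers every MHA-related admission. These are three different scopes for related outcomes.

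**The case against.** The best defence is that Table 1 lists measures, instruments and time points and is not an analysis specification. Summing days, handling zeros and choosing a count model are ordinary matters for a statistical analysis plan, which is not shown. Length of stay is also one of several secondary utilization measures, and admissions are reported beside it, so a reader could see fewer admissions next to longer stays. This stands for the choice of model and for any adjustment for earlier service use, and neither is raised here. It does not remove the core point, because the per-admission unit is stated in the article. The admissions outcome is only a partial safeguard, since its row names a narrower set of units than the length-of-stay row.

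Four stronger readings are tempting and are not supported.

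- A reader might infer that 30-day readmission is also compared only among people hospitalised after randomisation. The row gives no denominator, Section 2.6 speaks of participants in both groups, and discharge-enrolled participants can be compared as randomised. The base is undefined, not shown to be wrong.
- A reader might infer that an effective intervention will look harmful. That happens only if the averted admissions are mainly short; otherwise the bias is zero or flatters the intervention.
- A reader might think this reverses the forecast in Section 3. That forecast, "We also anticipate a 10–25% reduction in high-cost health service use (psychiatric readmissions and ED visits) among Text4Support participants", does not cover length of stay.
- A reader might conclude that acute psychiatric admissions go uncounted. The term for specialty units may include them, and Section 2.6 sets no unit limit. This is an inconsistency to settle, not a proven omission.

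**Conclusion.** The point holds for length of stay. As defined, the between-arm comparison conditions on admission after randomisation and cannot be read as an effect of the intervention. Under the assumed stays and 10-25% fewer admissions, the per-admission figure moves anywhere from about -24% to +24% while bed-days per randomised participant always fall, by about 3% to 13% where only short stays are averted. The sizes rest wholly on assumed stay lengths, an assumed half-and-half mix and a borrowed reduction. That the direction depends on which admissions are averted does not rest on those particular values.

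The index-stay rule, the readmission base and the unit list are gaps or inconsistencies in definition and carry less weight. These are secondary outcomes, so the change should be made, but the trial's primary clinical comparison is not affected.

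**What to change.** 1. Make the between-arm measure total MHA inpatient days per randomised participant over the 12 months from enrolment, with zero if never admitted and index-stay days excluded, analysed in all randomised participants. Keep length of stay per admission as a descriptive summary only.
2. For 30-day readmission, state the denominator and the index discharge. Compare discharge-enrolled participants from their index discharge, and report later discharges, in either entry route, separately.
3. Reconcile the units named in the admissions row with Section 2.6 and with the readmission row, so that it is explicit that acute psychiatric admissions are counted.

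The cost is wording in Table 1, Section 2.6 and the analysis plan. The days come from the same administrative extract, and no new data collection or extra participants are needed. The changes should be fixed before utilization data are compared by arm.

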** *Implementation outcomes (measures of process)* **							
**Reach**	Administrative data	The proportion of the target population who receive daily supportive text messages across Nova Scotia.	-	X	X	X	X
**Acceptability**	Self-designed instrument	Evaluates clients’ satisfaction and experiences with supportive text messaging programs.	-	X	X	X	X
**Appropriateness**	Sociocultural, gender and age sensitivity.	Qualitative in-depth interviews	-	X	X	X	X
**Incremental cost-utility**	Administrative data	The incremental cost-effectiveness ratio (ICER) is the ratio between the difference in costs and the difference in benefits of the intervention	-	X	X	X	X
**Overall satisfaction, retention, withdrawal, and engagement rate**	Self-designed Online survey	Evaluates clients’ satisfaction and experiences with supportive text messaging programs.		X	X	X	X

* Online, patient-completed scales. ** Clinician-rated scale.

## Data Availability

Data is available upon reasonable request to the submitting author.
